# Effectiveness of an 8-week overground walking with paretic lower limb loading on spatiotemporal gait parameters and motor function among chronic stroke survivors: a protocol for randomised controlled trial

**DOI:** 10.1186/s13063-022-07057-3

**Published:** 2023-02-20

**Keywords:** Gait symmetry, Lower limb loading, Overground walking, Randomised controlled trial, Spatiotemporal gait parameters, Stroke

## Abstract

**Background:**

Post-stroke gait deviations contribute to significant functional disability, impaired walking ability and poor quality of life. Prior studies suggest that gait training with paretic lower limb loading may improve gait parameters and walking ability in post-stroke. However, most gait training methods used in these studies are not readily available, and studies using cheaper methods are limited.

**Objective:**

The purpose of this study is to describe a protocol for a randomised controlled trial on the effectiveness of an 8-week overground walking with paretic lower limb loading on spatiotemporal gait parameters and motor function among chronic stroke survivors.

**Methods:**

This is a two-center, single-blind, two-arm parallel randomised controlled trial. Forty-eight stroke survivors with mild to moderate disability will be recruited from two tertiary facilities and randomly assigned into two intervention arms; overground walking with paretic lower limb loading or overground walking without paretic lower limb loading in a 1:1 ratio. All interventions will be administered thrice weekly for 8 weeks. Primary outcomes will be step length and gait speed whereas the secondary outcomes will include step length symmetry ratio, stride length, stride length symmetry ratio, stride width, cadence and motor function. All outcomes will be assessed at baseline, 4, 8 and 20 weeks after the start of intervention.

**Discussion:**

This will be the first randomised controlled trial to report the effects of overground walking with paretic lower limb loading on spatiotemporal gait parameters and motor function among chronic stroke survivors from low-resource setting.

**Trial registration:**

ClinicalTrials.gov NCT05097391. Registered on 27 October 2021.

## Background

Stroke remains the second leading cause of death and disability internationally and imposes a considerable personal and societal burden [1]. The health and economic costs associated with stroke are huge and alarming [2, 3]; thus, it poses a major public health problem and warrants development and implementation of optimal primary prevention and rehabilitation strategies to reduce the burden of the disease and its impact [1, 4].

The global incidence and prevalence of stroke have been estimated to be around 11.9 and 104.2 million, respectively [1] and expected to increase in the coming years, especially in low- and middle-income countries [5]. This is more problematic particularly in Sub-Saharan African countries due to limited resources and poor education on stroke risk factors and its warning signs besides the growing and ageing population [4, 6]. The crude prevalence and incidence rates of stroke in Nigeria have been reported to be 1460 per 100,000 and 25 per 100,000 person-years, respectively [7]. Moreover, stroke in Nigeria accounts for approximately 78% of neurological admissions [8], with mortality rates ranging between 21 and 45% [9–13]. The rising prevalence of stroke in Nigeria means the burden may continue to exacerbate pressure on the affected individuals, their families, health and economic systems [14, 15].

Stroke survivors typically exhibit varying neurological deficits and impairments including sensory, cognitive, perceptual, emotional, speech and motor abnormalities [16, 17]. The most important motor deficit post-stroke is hemiparesis contralateral to the cerebrovascular event [17]. This deficit reduces the capacity of the affected lower limb to maintain normal functions such as balance and initiation and control of movements, hence resulting in abnormal gait pattern (i.e. hemiplegic gait) [18, 19].

Post-stroke abnormal gait patterns contribute to significant functional disability, impaired walking ability and poor quality of life [20]. Gait asymmetry implies an imbalance in functional activities between two sides of the body or lower limb [21]. Post-stroke hemiparetic gait is caused by motor impairments such as altered muscle tone, lack of selective motor control, abnormal reflex, poor balance and weakness [22]. Asymmetrical spatial and temporal gait characteristics are common deviations observed in post-stroke hemiplegic gait. It has been documented that about 44–62% and 48–82% of stroke survivors exhibit asymmetry in spatial and temporal gait parameters, respectively [23, 24].

Observational studies have shown that post-stroke hemiparetic gait relative to the normal is significantly characterised by short step length and stride length, reduced cadence, low gait speed, increased step width, double support phases and asymmetric single limb loading [25–28]. After stroke, the paretic limb exhibits a prolonged period of swing and a reduced period of stance; as a result, decreased swing time and increased stance time are seen on the non-paretic limb [29]. These changes are believed to result from decreased walking speed as well as disturbances in other gait parameters between the paretic and non-paretic limbs which may limit gains from rehabilitation [30].

Gait asymmetry does not only affect gait quality in stroke but may also increase energy expenditure [31] and risk of falls [32] and causes loss of bone density of the hemiparetic lower limb [33]. Restoring gait symmetry is, therefore, a major goal for rehabilitation to enhance walking ability and safety, activities of daily living and quality of life among stroke survivors [34].

Despite rehabilitation efforts to improve gait in individuals with stroke, some patients still are unable to walk functionally [35–37]. It appears that many stroke survivors usually do not have significant improvement in gait function [38], and this is often due to inefficient weight application (limb loading) on the affected side causing non-linear limb load transfer [39]. Thus, it is conceivable that adding weight to the paretic limb may correct this imbalance and improve gait performance via an interlimb neural coupling mechanism [40]. Indeed, previous studies on healthy subjects indicate that the addition of small weights to limbs can enhance muscle activation [41, 42], balance ability [43] and walking factors such as distance, velocity and cadence [44].

A previous pretest-posttest pilot study conducted among individuals with chronic stroke found that the addition of a sandbag equivalent to 5% of body weight to ankle of paretic lower limb during weight-bearing treadmill training improved gait velocity, ability to climb stairs and increased ratio of swing phase of both paretic and non-paretic lower limb [45]. In a non-controlled study on chronic stroke patients, the addition of preferred cuff weight (0.7 kg or 1.1 kg) to ankle of paretic lower limb during aquatic treadmill walking decreased unwanted limb floatation and increased stance phase stability [46]. Similarly, in a recent pilot randomised controlled trial (RCT) to determine the effects of aquatic treadmill gait training with water-jet resistance versus underwater treadmill gait training with ankle weights in chronic stroke patients, both training methods improved static and dynamic balance and gait parameters including gait velocity, cadence, step length, stride length and swing phase with water-jet resistance training being more superior [47]. However, underwater treadmill may not be readily available and affordable in low-resource settings. Hence, there is need to devise low-cost and effective methods for gait retraining for stroke survivors in such contexts. It is worth noting that studies in the way of RCTs on the effect of overground walking with paretic lower limb loading in chronic stroke survivors are limited. Compared to underwater or land-based treadmill walk training, overground walk training is easy to perform and relatively cheaper and affordable.

The primary aim of this study is to determine the effectiveness of an 8-week overground walking with paretic lower limb loading compared with overground walking without paretic lower limb loading on step length and gait speed among chronic stroke survivors. The secondary aims were to compare the effects of these interventions on step length symmetry ratio, stride length, stride length symmetry ratio, stride width, cadence and motor function. We hypothesised that overground walking with paretic lower limb loading will have superior effects  on step length and gait speed compared with overground walking without paretic lower limb loading.

## Methods

### Ethical considerations

This study has been approved by the Health and Research Ethics Committee, Ministry of Health, Kano State, Nigeria (ref: NHREC/17/03/2018). The purpose and procedure of the study will be explained to all participants, and their written consent will be obtained.

### Study design

This study will be a single-blind, parallel group, two-arm, RCT with 1:1 allocation ratio. The time schedule of enrolment, interventions and assessments of participants are shown in Fig. 1. The study protocol is reported in line with the Standard Protocol Items: Recommendations for Interventional Trials (SPIRIT) 2013 Checklist (See Appendix I).

**Fig. 1 Fig1:**
[figure not shown]
Timetable for enrolment, interventions and assessments

### Study setting

The study will be conducted in the physiotherapy outpatient departments of Murtala Muhammad Specialist Hospital (MMSH) and Muhammadu Abdullahi Wase Teaching Hospital (MAWTH), Kano State, Northwestern, Nigeria.

### Training of research assistants

Six licenced physiotherapists (including the primary researcher) with at least five years of working experience in stroke rehabilitation will be engaged in the study. Three therapists including the primary researcher (first author) will be responsible for all aspects of the local organisation including identification, scheduling and screening of potential participants, as well as obtaining written informed consent. The primary researcher with another therapist will administer intervention to the participants. Another two therapists (not involved in screening or administration of intervention) will perform baseline and follow-up assessments. All the research assistants will receive a one-day training session, facilitated by the primary researcher, on the study procedures prior to the beginning of the study. They will be assessed to ensure conversancy and familiarity with the study procedures.

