### Randomisation and blinding

Upon completion of all the baseline assessments, consenting participants will be stratified by MRS scores (i.e. 1, 2 and 3) and randomised into two groups; overground walking with paretic lower limb loading or overground walking without paretic lower limb loading in a 1:1 ratio (Fig. 2) by a third party not involved in other aspects of the study. Allocation of participants will be concealed using consecutive numbered, sealed and opaque envelopes prepared using a web-based randomisation tool (available at https://www.sealedenvelope.com) with permuted block size of 6. All outcome assessors will be blinded to participants’ group allocation. However, it will be impossible to blind physiotherapists and participants considering the nature of the study interventions.

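### The primary researcher both recruits and gives the unblinded treatment, with one fixed block size of 6, so some later allocations (at most about 19–25% with certainty) could be inferred despite sealed envelopes

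*Protocol article*

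**What the plan says.** Under Training of research assistants, the Protocol article gives three therapists, one of them the primary researcher, a joint recruiting role: they "will be responsible for all aspects of the local organisation including identification, scheduling and screening of potential participants". Taking consent falls to the same three. The same section then says: "The primary researcher with another therapist will administer intervention to the participants". Role separation is stated for the outcome assessors only: "Another two therapists (not involved in screening or administration of intervention) will perform baseline and follow-up assessments". No such rule separates those who recruit from those who treat.

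Under Randomisation and blinding, patients are stratified on MRS scores 1, 2 and 3 and allocated 1:1 by an independent third party. The envelopes are serially numbered, opaque and sealed, and were prepared "with permuted block size of 6". Allocation follows consent and all baseline assessments. Of the treating staff the article says that "it will be impossible to blind physiotherapists and participants considering the nature of the study interventions".

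**The concern.** Sealed envelopes hide the next allocation from someone who has no other information. They do not hide it from someone who can count. With one block size, a person who knows that size, the patient's stratum and the earlier allocations in that stratum can sometimes work out what comes next. The primary researcher is described as the article's first author, so this recruiter knows the block size, and as a treating therapist also sees at least some allocations.

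What is at stake is selection: who is approached, when they are enrolled, or which MRS stratum they are placed in. Blinded outcome assessment protects the measurement of enrolled patients. It does not protect the choice of whom to enrol.

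**Working it through.** **Inputs.** Block of 6 at 1:1, so 3 + 3, and three MRS strata (Randomisation and blinding). 48 patients, 24 per group (Sample size calculation). The article does not spell out that blocks are formed within strata, but stratified permuted-block randomisation implies it. The split of patients over the strata is not given and is assumed below.

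**One full block.** There are C(6,3) = 20 equally likely orders.
- The 4th allocation is certain if the first three are alike: 2/20 = 0.10.
- The 5th is certain if the last two are alike: 8/20 = 0.40.
- The 6th is always certain. The first three never are.
- Expected number certain: 0.10 + 0.40 + 1 = 1.5 of 6, or 25%.

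The best guess is the arm with more places left in the block, or a coin toss if they are equal.

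| Position | Probability that the guess is right |
|---|---|
| 1 | 0.5 |
| 2 | 3/5 = 0.6 |
| 3 | 0.4 × 0.75 + 0.6 × 0.5 = 0.6 |
| 4 | 0.1 × 1 + 0.9 × 2/3 = 0.7 |
| 5 | 0.4 × 1 + 0.6 × 0.5 = 0.7 |
| 6 | 1.0 |
| Sum | 4.1 of 6, or 68.3% |

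**Whole trial, three lists.**

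| Split (assumed) | Certain | Correct guesses |
|---|---|---|
| 16/16/16 | 3 × (2 × 1.5 + 0.1) = 9.3 (19%) | 3 × (2 × 4.1 + 2.4) = 31.8 (66%) |
| 8/20/20 | 7 × 1.5 = 10.5 (22%) | 7 × 4.1 + 3 × 1.1 = 32.0 (67%) |
| 6/18/24 | 8 × 1.5 = 12.0 (25%) | 8 × 4.1 = 32.8 (68%) |

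Here 2.4 and 1.1 are the sums of the first four and first two rows of the guessing table. A simulation of 3,000 runs per split agrees (9.33, 10.54 and 11.95 certain).

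**Randomly varied block sizes.** The same simulation, with a guesser who knows the set of sizes in use, gives:
- sizes 4/6/8: about 1.0–1.2 certain (2–3%), best guess right about 67%;
- sizes 2/4/6: about 1.7 certain (4%), best guess right about 70%.

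Varying the sizes removes nearly all certainty and leaves guessing about as good as before.

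**From prediction to bias.** Suppose enrolled patients differ by +δ or −δ according to the guess (δ is assumed; the article gives no basis for a value). The raw difference between arms shifts by δ × (correct − incorrect guesses)/(patients per arm).
- Full blocks: (4.1 − 1.9)/3 = 0.73. With δ = 0.10 or 0.25 SD the shift is 0.07 or 0.18 SD.
- 16/16/16: (31.8 − 16.2)/24 = 0.65. The shift is 0.065 or 0.16 SD.
- If the primary researcher recruits one third of patients (assumed) and only that person guesses, 0.65/3 = 0.22. The shift is about 0.02 or 0.05 SD.

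**Through the planned model.** The Statistical analysis section fits time with baseline as reference, treatment, and their interaction. The interaction compares changes from baseline. If selection moves a patient's stable level by s, then (Y_t + s) − (Y_0 + s) = Y_t − Y_0, and the shift cancels. A simulation with three strata of 16 and a fully informed guesser gave a raw bias of 0.064 or 0.165 SD, and about 0.00 in the change from baseline.

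**The case against.** Three objections have force.

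First, the safeguards are better than in many small trials: a third party randomises, the envelopes are numbered, opaque and sealed, and allocation comes only after consent and baseline. The article already has MRS and baseline outcomes recorded before randomisation, so nothing need be added there. All this stands, but these measures protect the unopened envelope and do not prevent inference from allocations already seen.

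Second, the predictability figures assume one recruiter who knows every earlier allocation in the stratum. The article names three recruiters, two treaters and two centres, and does not say whether lists are shared between centres. The primary researcher may see only part of each sequence. This also stands, so the figures are upper bounds. Nor do the documents say who scores the MRS. As it is an eligibility criterion, scoring by the recruiters is a fair inference but no more.

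Third, a reader might infer that the treatment estimate is biased by 0.07 to 0.18 SD. The documents do not support that. The figure belongs to a raw follow-up difference, with one person recruiting everyone and seeing every allocation, and with a shift that is assumed. A shift in stable level largely cancels in the planned baseline-referenced interaction.

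On timing, recruitment was expected to end by February 2023, the month of publication, although the article describes it as ongoing. Few or no patients may remain to be enrolled.

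**Conclusion.** The point holds as a moderate design weakness. Two choices that the article states, the recruiter-treater overlap and a single block size within MRS strata, allow partial prediction: at most about 19–25% of allocations with certainty, and a best guess right about 66–68% of the time against 50% by chance. A reader might go further and conclude that concealment has failed or that most allocations are known. The arithmetic does not support this, since at least three quarters remain uncertain even to a fully informed recruiter.

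Nothing in the article shows that selection took place. Prediction would bias the treatment effect only if recruiters selected on expected improvement, which change from baseline does not remove, or if a follow-up difference were reported without baseline adjustment. The article calls its effect an adjusted between-group difference without saying adjusted for what, so the second route is not closed by the text. The conclusion assumes that blocks run within strata and that the two other recruiters do not treat. The count of six staff suggests the latter: three recruiters, one further treating therapist and two assessors.

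**What to change.** **If enrolment continues.** Have the other two recruiting therapists do the screening, MRS scoring and consent, without being told past allocations, and limit the primary researcher to treatment. This removes the route to both certain prediction and guessing. It needs no new staff; the small cost is more screening work for those two.

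As a secondary step, have the third party prepare the unused envelopes again with randomly varied block sizes that are not disclosed to the team. This takes one rerun of the web-based tool. It cuts certain predictions to about 2–4% but does not meaningfully lower the best-guess rate, so it does not replace the separation of roles.

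**If enrolment has closed.** State in the trial report that one person both recruited and treated and that the block size was fixed at 6. Report baseline balance by MRS stratum and by order of enrolment. Base the treatment effect on a baseline-adjusted contrast, such as the time × treatment interaction already planned, and say so explicitly. The cost is a few lines of text and one table.

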### Participants’ recruitment

The study participants will be drawn from a population of patients with stroke referred for outpatient physiotherapy at MMSH and MAWTH in Kano State. They will be given all the necessary information about the procedures and potential benefits of the study. Written informed consent will be obtained from all the participants after assessment for eligibility. To be eligible for the study, patients must meet the following criteria: (1) unilateral ischemic or hemorrhagic stroke occurring at least 3 months before enrolment; (2) male or female between the age of 20 and 70 years; (3) Having Modified Rankin Scale (MRS) scores of 1, 2 or 3 and also able to walk at least 10 m independently without assistive device; and (4) ability to follow verbal instructions. Patients with one or more of the following criteria will be excluded from the study: (1) cognitive impairments; (2) visual impairments; (3) musculoskeletal disorders that may affect gait such as arthritis; (4) other neurological disorders such as Parkinson's disease, multiple sclerosis; (5) cardio-respiratory conditions that may limit participation such as atelectasis; and (6) concurrent participation in other interventional clinical trials.

Demographic and clinical characteristics such as age, gender, marital status, education level, occupational level, duration of stroke, laterality, leg dominance, blood pressure, weight, height, body mass index (BMI), side of affectation and MRS scores will be obtained using a prepared study proforma. Assessment of baseline outcome variables will be then conducted prior to randomisation. A specific ID will be given to all participants for recognition.

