### Statistical analysis

Descriptive statistics of mean, standard deviation, percentage and frequency will be used to summarise the data. Comparison of baseline categorical variables among groups will be conducted using Fisher’s exact test or chi-square test and for continuous variables using independent *t*-test or Mann–Whitney *U* test where applicable. Intention-to-treat principle will be used for the primary statistical analysis by including each participant’s available data in accordance with original allocation and irrespective of the level of attendance. The primary and secondary outcomes will be analysed using linear mixed-effects models (LMMs) by including time (4, 8 and 20 weeks, baseline will be the reference), treatment (overground walking with paretic lower limb loading and overground walking without paretic lower limb loading) and a time × treatment interaction as fixed effects, and a random intercept to account for within-subject correlations. Treatment effect will be defined as the adjusted between-group difference and the associated 95% confidence intervals (CI). We opted to use LMMs because it provides unbiased estimates when data are missing at random [59]. Additionally, per-protocol analysis using the LMMs will be performed as sensitivity analysis by excluding randomised participants who did not received allocated intervention, or who attended fewer than 18 treatment sessions, received proscribed concomitant intervention known to influence gait, and experienced exclusionary medical conditions listed in the study exclusion criteria. All the statistical procedures will be performed using SPSS version 23.0 (IBM Co., Armonk, NY, USA) at a probability level of 0.05.

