## Discussion

To our knowledge, no other study in the way of RCT determined the effectiveness of applying additional weight to paretic lower limb during overground walking training on gait ability and motor function compared to overground walking training without paretic lower limb loading among chronic stroke survivors. Individuals with hemiparesis following stroke demonstrate a wide range of spatiotemporal gait abnormalities [25, 26, 60, 61], which in the long run may result in more dependency in basic activities of daily living and consequently reduced quality of life [62]. Improving walking function is therefore the most desired goal of stroke rehabilitation [63] and can be regarded as a yardstick for evaluation [25, 55].

Despite rehabilitation efforts, up to 80% of stroke survivors still experience impaired walking function and further 22% do not regain any walking function [64]. Previous studies [46, 47] found that the addition of weight to paretic lower limb during aquatic walking positively influences spatiotemporal gait parameters of chronic stroke survivors, however, these studies may not be generalised because buoyancy may have influenced some gait outcomes. Another limitation is that they suffered a small sample size with one of them being a non-controlled trial [46]. Moreover, underwater treadmill walking was used for gait training, which may not be readily available and affordable in low-resource settings like Nigerian clinics. This ultimately poses a major challenge, particularly in rural areas where the majority of stroke patients reside [48]. This trial will be therefore conducted to determine the effectiveness of an 8-week, low-cost overground walking with paretic lower limb loading among chronic stroke survivors. Paretic limb loading during overground walking approach could be safe and more accessible as well as affordable compared with aquatic treadmill training.

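### The aim speaks of chronic stroke survivors, but entry is open from 3 months after stroke with the label undefined, and recorded time since stroke is not in the listed effect model

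*Protocol article*

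**What the plan says.** The Objective in the abstract concerns the "effectiveness of an 8-week overground walking with paretic lower limb loading on spatiotemporal gait parameters and motor function among chronic stroke survivors". The primary aim at the end of the Background compares the two arms "on step length and gait speed among chronic stroke survivors". The Discussion says that the trial tests "low-cost overground walking with paretic lower limb loading among chronic stroke survivors". The title names the same population.

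Under Participants' recruitment, the only criterion on timing is "unilateral ischemic or hemorrhagic stroke occurring at least 3 months before enrolment". There is no upper limit. The article does not define *chronic* or explain the choice of 3 months. The same section puts "duration of stroke, laterality, leg dominance" on the baseline proforma.

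Under Randomisation and blinding, the only stratification factor is the Modified Rankin Scale score. Under Statistical analysis, the fixed effects are time, treatment and their interaction, with "a random intercept to account for within-subject correlations". The treatment effect is called adjusted, but no baseline covariate is named. Continuous baseline variables are to be compared between groups, which by implication includes duration of stroke.

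**The concern.** The label and the entry rule do not describe the same thing unless *chronic* means at least 3 months after stroke, and the article does not say that. One rule admits a patient 3 months after stroke and a patient several years after stroke. A reader of the eventual report could not tell whom the conclusion covers.

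The second part is efficiency. If recent entrants improve faster than the rest, gait outcomes will spread more within each arm. A random intercept absorbs differences in level between patients but not differences in rate of change. The variable that could account for some of that spread is collected and then left out of the listed model. With 24 patients per group, avoidable variance is worth removing when it costs almost nothing.

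**Working it through.** **Inputs from the article.** Minimum time since stroke 3 months (Participants' recruitment); visits at baseline and at 4, 8 and 20 weeks (Outcome assessments and follow-ups); 24 per group and a correlation of 0.5 among repeated measures (Sample size calculation). The plan gives no figure of its own on time since stroke beyond the 3 months, so there is none to reproduce.

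**Assumed inputs, not in the article.** A share p of 0.1 to 0.5 of participants are early entrants. They improve by r = 0.25 to 1.0 outcome SD more than the others.

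**Step 1: timing.** At 4.345 weeks per month, a patient who enters at month 3 is at 3 + 8/4.345 = 4.8 months at week 8, and at 3 + 20/4.345 = 7.6 months at week 20.

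**Step 2: bias.** Both arms are randomised 1:1 and run concurrently, so each gains the same expected extra change, p × r. This runs from 0.1 × 0.25 = 0.025 SD to 0.5 × 1.0 = 0.50 SD. It cancels in the expected between-group difference.

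**Step 3: variance.** A mixture of two groups with shares p and 1 − p and means r apart adds r²p(1 − p) to a variance of 1. The variance factor is V = 1 + r²p(1 − p), and the standard error rises by √V − 1. At a correlation of 0.5 the variance of change from baseline is 2 × (1 − 0.5) = 1, so the same factor applies to change scores. A nominal 80% power becomes Φ((1.960 + 0.842)/√V − 1.960).

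| p | r (SD) | V | SE increase | Power |
|---|---|---|---|---|
| 0.1 | 0.25 | 1.006 | 0.3% | 79.8% |
| 0.1 | 1.0 | 1.090 | 4.4% | 76.5% |
| 0.3 | 0.5 | 1.052 | 2.6% | 78.0% |
| 0.5 | 0.5 | 1.062 | 3.1% | 77.6% |
| 0.5 | 1.0 | 1.250 | 11.8% | 70.7% |

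**Step 4: chance imbalance.** The difference between arms in the share of early entrants has variance 2p(1 − p)/24. Its effect on the estimate has variance r² × 2p(1 − p)/24. The variance of the difference without it is 2/24. The ratio is r²p(1 − p), which is exactly V − 1 from Step 3. The two are one quantity seen from two sides.

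**Step 5: parameters.** Log months since stroke is one term. Its interaction with three follow-up visits (baseline as reference) is three more, so four per outcome. The interaction is the part that matters: with complete data, a covariate that enters only as a constant shift leaves the estimated differences in change from baseline as they were.

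**The case against.** The strongest reply is that nothing in the article makes 3 months too early to count as chronic. It defines no phase, shows no recovery curve and never mentions 6 months. That stands. A reader might infer that the entry rule contradicts the label, but that needs an outside convention. What the article does show is a label left undefined over a bare 3-month threshold.

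A reader might also infer that natural recovery confounds the treatment comparison. It does not: the control group receives the same programme at the same time without the weight, and the article defines the treatment effect as a between-group difference. Nor is time since stroke wholly unused, since it falls under the planned baseline comparison. That comparison, however, does not adjust the estimate.

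A third tempting reading adds a chance shift of up to 1.96 × 0.144 × 1.0 = 0.28 SD to the variance increase. That is the 95% limit of the most extreme scenario, and Step 4 shows that it is already in the variance.

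Finally, covariate lists often sit in an analysis plan that is not shown, and the word adjusted may point to one. A missing list alone would be no finding. Here the article does enumerate the model terms, and the population wording does not depend on any analysis plan. Stratifying on disability is a defensible choice; more strata with blocks of 6 and 48 patients would leave many blocks incomplete.

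**Conclusion.** The point holds as one of population wording and modest efficiency. That the label is undefined, that entry opens at 3 months, and that duration of stroke is neither a stratification factor nor a listed model term can all be read directly from the article. The primary contrast is unbiased.

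The loss of precision is conditional. Over the assumed ranges it runs from negligible (SE up 0.3%) to moderate (SE up about 12%, power from 80% to about 71%). The article cannot show where in that range the trial falls, and the share of early entrants could be close to zero. The wording issue does not depend on these assumptions. Both changes are cheap enough to be worth making before analysis.

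**What to change.** 1. Reconcile the label with the entry rule. Either state the population in the aim, and later in the report's conclusions, as stroke survivors at least 3 months after stroke, or define *chronic* and justify the 3-month threshold.

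2. Before analysis, prespecify baseline time since stroke (for example log months) and its interaction with visit as covariates for step length and gait speed. Say that this is part of what adjusted means.

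An analysis without the most recent strokes is optional and supportive only. A 6-month cut would be an outside convention and should be declared as such. On the assumptions above it could also remove up to half the sample.

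The cost is about four extra parameters per outcome and a less tidy population label. No new data are needed and recruitment, which the article reports as under way, does not change. The gain in precision is at most the loss in the table, and smaller if log months captures recovery only in part.
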